### Study Sample

A protocol for the veterans’ RCT of the DrinksRation app calculated a sample size of 37 participants in each arm to achieve significance and a target of 620 invitations to cover nonparticipation and attrition [17]. Assessing the sample size for a serving (nonveteran), non–help-seeking population, an effect size of 4 units of alcohol per week, and a mean consumption of 30.5 (SD 14.9) units/week were used. Consumption is based on a large systematic review of face-to-face ABIs [21]. The mean change of 4 units is based on a change of 2 units detected in a systematic review for the general population [21]; 7 units detected in a previous DrinksRation study [16]; and 4 units being used in the help-seeking veteran RCT [17]. The sample size was calculated as 218 per arm. The study will aim to recruit 728 participants to allow for a 40% attrition rate. Defense statistics state that 59% of the serving AF population are at risk of alcohol-related harm [6]. This equates to approximately 7250 personnel per month having a PDI and being eligible for the study.

### Recruitment

Potential participants for the MDR study will be currently serving UK AF personnel identified through PDIs and self-identification following study publicity. All 148,000 serving military personnel are offered PDI at least annually. Before the PDI, all personnel are asked to complete an AUDIT-C screening tool. Those scoring at increasing risk of alcohol-related harm to health (≥5) are given an alcohol brief intervention by the dental staff, which consists of a single brief discussion around the risks of drinking lasting 2-3 minutes. Those scoring in the higher risk group (8-10) or suggesting possible dependence (11-12) are offered a referral from the dentist to a general practitioner for follow-up.

The trial will be publicized through service-specific communications, social media, and recruitment posters displayed across the UK defense estate. Additionally, potential participants will be identified through service-specific communication, including links and QR codes to the study website promoted through single service information pathways and on the defense intranet. MyNavy and similar apps within the defense gateway will also be used to announce the trial and direct potential participants to the study website. Military-focused social media, such as #MilTwitter and AF-specific Facebook groups, will be asked to promote the study and host links to the study website. Posters with a short link and QR code for the study website will also be displayed in areas of high footfall in large establishments.

All potential participants will be screened for eligibility using a web-based AUDIT-C tool [13] on Research Electronic Data Capture (REDCap) [22]. Those scoring ≤4 will not be eligible for the DrinksRation RCT. Personnel scoring ≥5 will be given an ABI either in the form of the standard defense guidance on reducing alcohol use or by the dental staff as per usual management. Personnel will then be directed to the participant information sheet (PIS), eligibility criteria, and web-based consent form on REDCap.

Participants will be included in the study if they are currently serving UK AF; have an Android or iOS smartphone and are willing or able to download the DrinksRation app; report an AUDIT-C score of ≥5; and provide a telephone number or email address for participant safety purposes.

Participants will be excluded if they are unwilling or unable to download the DrinksRation app or if they scored ≤4 on AUDIT-C. There will be no exclusion on the grounds of harmful drinking identified by AUDIT-C screening.

There are no age or sex restrictions on participation beyond those of the military population. Specifically, personnel aged 18 years or younger are not excluded from the MDR study, as they form a small proportion of the UK military population. While the purchase of alcohol by those aged 18 years or younger is illegal, consumption by underage personnel does happen, and age does not proffer any immunity against potentially harmful drinking behaviors [23]. Indeed, living with people who are drinking alcohol increases the likelihood of a child drinking (odds ratio 3.6 for children living with 3 or more drinkers) [3].

After consenting to inclusion in the study and the collection of baseline demographics, participants will be randomized to the intervention group or TAU group using the embedded REDCap randomization module.

### Intervention

Participants randomized to the intervention arm of the RCT will be sent an email link to the DrinksRation app with a unique reference code to enable data linkage between REDCap and DrinksRation. The app’s function, theoretical basis, and supporting evidence are fully described elsewhere [16,20,24]. Images of the app and its functionality are shown in Figure 1. After downloading the app, on first use, participants will be prompted to complete baseline assessment surveys. App usage and further surveys were then presented by the app with push notifications to the participant, highlighting the need for completion. Participants will be asked to use the app for a minimum of 28 days. Participant flow through the study is shown in Figure 2.

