### Control

Participants randomized to the control arm will receive baseline assessment and all further surveys through email with the same periodicity as the intervention group. The control group will be asked to complete the surveys and will be given access to the DrinksRation app at the end of the study period. Noncompletion of surveys will prompt an automated push notification (intervention arm) or email (control arm) reminder after 24 hours. The structural difference between the arms was considered unavoidable due to the difficulty of creating a sham digital psychological intervention [25]. If a pared-down “dumb” version of the app were offered to the control arm, then it would be difficult to determine whether any effect was due to the visibility of the app or interaction with the app. A previous study of the DrinksRation app showed a large attrition rate in the control arm when participants were given a dumb version of the app [20].

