### Measures

The primary outcome measure is a change in alcohol units consumed per week between baseline and day 84, as measured by the timeline follow-back method [27]. Secondary outcomes are a change in the Alcohol Use Disorders Identification Test (AUDIT) score, a change in the quality of life assessment, and a change in drinking motivations and app useability. While the DrinksRation intervention aims to reduce alcohol intake at 84 days, a final data collection at 168 days will assess any persistent benefits.

Data will be collected through a selection of surveys pushed to the participants in line with the periodicity detailed in Table 1.

The study instruments are all validated for the general population and are detailed in Table 1. The alcohol and mental health symptomatology surveys were included in the veteran’s trial. The MDR trial additionally includes surveys for drinking motivations (Drinking Motives Questionnaire 9-item tool [DMQ-R]), recent life events (Recent Life Events Questionnaire [RLE-Q]), gambling motives (Gambling Motivations Questionnaire [GMQ-9]), and domestic abuse and sexual assault (National Crime Survey for England and Wales). These behaviors have been associated with both alcohol consumption [3] and a military population [40,41]. A tertiary outcome of the MDR study is to assess the correlation of these issues with alcohol use within the military population. This information does not contribute to the assessment of the app’s effectiveness, but it is valuable information for UK defense policy makers.

**Table 1 table1:** Summary of measures and data collection time points.

Measure	Total questions	Day 0	Day 0-1	Day 3	Day 7	Day 28	Day 84	Day 168
Demographics	18	✓						
AUDIT-C^a^ [13]	3	✓						
Participation information and consent	N/A^b^	✓						
Alcohol use (AUDIT^c^) [28]	10		✓			✓	✓	✓
Alcohol intake (TLFB^d^) [27]	N/A		✓			✓	✓	✓
Resource allocation (YAACQ^e^) [29]	24		✓				✓	✓
Readiness to change ruler	1		✓					
Self-efficacy ruler	1		✓					
Depression (PHQ-2^f^) [30]	2		✓			✓		
Anxiety (GAD-2^g^) [31]	2		✓			✓		
International trauma questionnaire for PTSD^h^ (PC-PTSD-5^i^) [32]	5		✓			✓		
World Health Organization Quality of Life-BREF^j^ (WHOQOL-BREF) [33]	27			✓		✓	✓	✓
Loneliness (De Jong Gierveld) [34]	11			✓		✓		
Drinking motivations (DMQ-R^k^) [35]^l^	20			✓			✓	
Recent life events (RLE-Q^m^) [36]^l^	21			✓				
Gambling motives (GMQ-9^n^) [37]^l^	9				✓			
Domestic abuse (NCSE&W^o^) [38]^l^	30				✓			

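### Baseline alcohol intake for the primary outcome is collected after randomisation and, in the intervention arm only, depends on opening the app, so it is not protected by randomisation

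*Protocol article*

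**What the plan says.** The Measures section fixes the endpoint: "The primary outcome measure is a change in alcohol units consumed per week between baseline and day 84, as measured by the timeline follow-back method".

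The order of procedures can be read from four places in the protocol article:

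- Recruitment, on screening: "All potential participants will be screened for eligibility using a web-based AUDIT-C tool". This is done on REDCap and is the only alcohol measure that precedes allocation.
- Recruitment, on allocation: "After consenting to inclusion in the study and the collection of baseline demographics, participants will be randomized to the intervention group or TAU group".
- Intervention: "Participants randomized to the intervention arm of the RCT will be sent an email link to the DrinksRation app with a unique reference code". The next step is "After downloading the app, on first use, participants will be prompted to complete baseline assessment surveys".
- Control: "Participants randomized to the control arm will receive baseline assessment and all further surveys through email".

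Table 1 agrees. Demographics, AUDIT-C and consent are ticked under Day 0. TLFB and the full AUDIT are ticked under a separate Day 0-1 column and again at days 28, 84 and 168. Data Management and Confidentiality adds that data sit in REDCap or in the app according to arm. Under Control and Data Monitoring, a missed survey triggers one reminder after 24 hours, by push notification in the intervention arm and by email in the control arm, and nothing further. The Statistical and Analysis Plan section promises intention-to-treat, multiple imputation where appropriate, and a repeated-measures mixed model.

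**The concern.** A baseline taken before allocation has the same expected distribution in both arms and cannot be affected by assignment. A baseline taken after allocation has neither guarantee. Here it is the starting value of the primary outcome, so an arm difference in who completes it or how it is answered can enter the treatment comparison.

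The two arms also face different conditions for having a baseline at all. A control participant must answer an emailed survey. An intervention participant must follow an emailed link, install the app, open it and then answer. The intervention arm's reminder is a push notification, which as described cannot reach someone who has not installed the app. Later surveys in that arm also come through the app, so a person who never opens it lacks both the baseline and the day-84 value. Missingness would then follow both arm and engagement.

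**Working it through.** **The plan's own figures.** Inputs from Study Sample: difference 4 units/week, SD 14.9, 40% attrition. Two-sided alpha of 0.05 and 80% power are assumed, since sidedness and power are not stated.

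n per arm = 2 × (1.96 + 0.8416)² × 14.9² / 4² = 217.8, rounded up to 218. Then 218 / 0.6 = 363.3, rounded up to 364 per arm and 728 in total. Both stated figures reproduce.

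**Stable route difference.** Suppose reporting in the app differs from reporting by email by a constant m. The intervention arm uses the app at baseline and at day 84, so its change contains m − m = 0. A constant route difference drops out of the change score.

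**Shift confined to baseline.** If reported baseline in one arm is off by b and day 84 is not, the difference in mean change is off by b. With b = 1, that is 1/4 = 25% of the target. With baseline adjustment the bias is about rho × b, where rho is the baseline to day-84 correlation (not given).

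To show scale, take 218 analysed per arm and assume the change has SD 14.9. Then SE = 14.9 × √(2/218) = 1.43, and P(reject) = 1 − Φ(1.96 − d/SE) + Φ(−1.96 − d/SE), with d the true effect plus or minus b. All values of b are assumptions.

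| b (units/week) | Rejection rate, no true effect | Power at 4 units, adverse shift | Power at 4 units, favourable shift |
|---|---|---|---|
| 0 | 5% | 80% | 80% |
| 0.5 | 6.4% | 69% | 88% |
| 1 | 10.8% | 56% | 94% |
| 2 | 28.9% | 29% | 99% |

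**Never opening the app.** The protocol gives no rate. Assuming 5% to 25% of 364: 0.05 × 364 = 18 and 0.25 × 364 = 91 people with no TLFB at any visit.

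If a fraction u never open the app and their change differs from that of openers by D, the mean change among openers differs from that of the whole arm by u × D. Taking D from 2 to 7 units (assumption, borrowing the range of changes mentioned in Study Sample):

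- u = 5%: 0.05 × 2 = 0.1 to 0.05 × 7 = 0.35 units
- u = 25%: 0.25 × 2 = 0.5 to 0.25 × 7 = 1.75 units

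This is the gap that imputation would have to close using AUDIT-C and demographics.

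**The case against.** The strongest reply is that each arm keeps one route throughout, so the difference between app and email is not in itself a source of bias in change. That stands. A reader might infer from the two routes alone that the primary outcome is biased; the document does not support that. The table above applies only to a shift present at baseline and absent at day 84.

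Second, TLFB is retrospective, the nominal window is one day, and the app asks for the baseline on first use before its other content. True prior intake should hardly move and exposure to the app is slight. This limits the reporting problem. It does not deal with selective completion, and no rule is given for a late first use.

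Third, a reader might infer that everyone reports baseline knowing their allocation. Randomization and Blinding says participants were told only that the research involved completing surveys. That is hard to square with an eligibility criterion naming the app and with only one arm receiving it, but knowledge of allocation, in the control arm especially, is not established.

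Fourth, a reader might infer that intention-to-treat cannot be honoured. The plan does retain those lost to follow-up and does foresee multiple imputation. The fair criticism is that, for those who never open the app, the imputation would be weakly informed.

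Fifth, people unwilling or unable to download the app are excluded, which should lower non-opening, and controls too can ignore an email. Both points stand; they reduce the likely size but leave the extra step in one arm.

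**Conclusion.** The concern holds in limited form. The text and Table 1 agree that the baseline of the primary outcome is taken after allocation and, in the intervention arm only, depends on downloading and opening the app. No pre-randomisation TLFB is described anywhere in the article (the flow diagram is not shown). The comparison is therefore open to selective completion and to any reporting shift specific to baseline.

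Neither the size nor the direction of bias can be determined from the document. The 1-unit shift (25% of the target effect) and the 5% to 25% non-opening rate (18 to 91 of 364) are assumptions used to show scale. Analysis can soften the problem but cannot restore a randomisation-protected baseline afterwards, and the remedy is cheap, so it is worth changing the procedure.

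**What to change.** 1. Collect TLFB and AUDIT from everyone in the REDCap session after consent, and release the randomisation module only when TLFB is complete.
2. Define baseline in the primary outcome as that value, and drop the baseline prompt in the app.
3. Send the day-84 and day-168 TLFB to both arms by the same emailed REDCap link. Without this step the intervention arm alone would move from REDCap to the app between baseline and follow-up, and a route difference that now cancels would enter the outcome. It also lets people who never open the app supply the day-84 value, which an earlier baseline alone would not achieve. The follow-up AUDIT, and the day-28 TLFB if it enters the mixed model, should follow the same route for the same reason.

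The cost is at most the 13 minutes that Table 1 allows for the whole Day 0-1 set, moved ahead of allocation. Some people will drop out at that point, but before randomisation this does not bias the comparison. There is also a small configuration change in the app and in REDCap, and an ethics amendment. The targets of 218 per arm and 728 in total are unaffected.

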**Figure 1 figure1:**
[figure not shown]
Military DrinksRation randomized controlled trial: smartphone app screenshots.

**Figure 2 figure2:**
[figure not shown]
Study flow diagram. Primary and secondary outcomes are assessed at day 84, with outcomes reassessed at day 168 in order to understand the longer-term benefits of the intervention. AUDIT-C: Alcohol Use Disorders Identification Test for Consumption; REDCap: Research Electronic Data Capture.

### Control

Participants randomized to the control arm will receive baseline assessment and all further surveys through email with the same periodicity as the intervention group. The control group will be asked to complete the surveys and will be given access to the DrinksRation app at the end of the study period. Noncompletion of surveys will prompt an automated push notification (intervention arm) or email (control arm) reminder after 24 hours. The structural difference between the arms was considered unavoidable due to the difficulty of creating a sham digital psychological intervention [25]. If a pared-down “dumb” version of the app were offered to the control arm, then it would be difficult to determine whether any effect was due to the visibility of the app or interaction with the app. A previous study of the DrinksRation app showed a large attrition rate in the control arm when participants were given a dumb version of the app [20].

### Randomization and Blinding

Participants will be randomized using the in-built randomization module of the REDCap program. This module automatically allocates participants to either the DrinksRation app or the TAU group based on a randomization table generated on the internet using the Sealed Envelope website [26]. Two participant blocks in a 1:1 ratio will be used. Randomization will be stratified by sex because it has previously been shown that alcohol use in the UK military is different between the sexes [4]. The randomization module will be programmed by the study independent medical officer (IMO), who is not blinded to the allocations in order to enact the safety protocols if required. The researchers had no visibility of programming, and role-based access to REDCap prevented access to any identifiable information or allocation for the research team. There was no contact between researchers and participants at any stage of the trial.

Participants were blinded to the intervention as they were told that the research involved them completing various surveys about drinking behaviors, health, and well-being. The study IMO will not be blinded to allocation and will have data access rights allowing him to link the participant reference codes to personal identifiers in case of any adverse events.

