### Study Design

The MDR study is a 2-arm, single-blind, 1:1 RCT of the UK AF population comparing the effectiveness of the DrinksRation smartphone app with treatment as usual (TAU) for those at risk of alcohol-related harm. It is hypothesized that the DrinksRation app will be more efficacious at reducing alcohol consumption compared to TAU.

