### Adverse Events

The investigators will review the data weekly to identify any potential adverse events. As per the veteran’s DrinksRation study, an adverse event is defined as a participant either consuming more than 25 units of alcohol in a 24-hour period or giving survey responses suggesting a significant mental health problem [17]. Additionally, participants can register an adverse event or problem by contacting the researchers through the study email address or website.

If an adverse event is identified, the principal investigator (PI) will review the available data for the participant, and if there are concerns, the PI will inform the IMO. The IMO will have access to the patient identifiable information and will contact the patient to facilitate referral to primary care if required and assess suitability to continue in the trial. Figure 3 details the adverse event management plan. All adverse events will be recorded in a risk event log held within the REDCap research database.

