Participants are able to withdraw from the study at any point up to the point when the data capture is extracted for analysis. At this point, the data will be grouped, and it will no longer be possible to select individual data. Withdrawal from the intervention arm is managed entirely from within the DrinksRation app. Participants visit the “Settings” tab, and the option to withdraw is visible (see Figure 4 below). To withdraw from the control arm, participants will need to email the PI, either directly or through the study website. Withdrawing participants are given the option to delete the data already collected or allow the research team to use this data.

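### The trial is labelled single-blind with blinded participants, but its eligibility and delivery rules let participants tell their arm, and the primary outcome is their own report

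*Protocol article*

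**What the plan says.** The Abstract and Study Design label the trial single-blind; Study Design reads: "The MDR study is a 2-arm, single-blind, 1:1 RCT of the UK AF population comparing the effectiveness of the DrinksRation smartphone app". Randomization and Blinding makes three claims:

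- Participants are blinded: "Participants were blinded to the intervention as they were told that the research involved them completing various surveys about drinking behaviors".
- The research team is kept from allocation: "role-based access to REDCap prevented access to any identifiable information or allocation for the research team".
- Researchers and participants have no contact at any stage.

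The same section says that the IMO is not blinded.

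Other sections describe what participants see and do:

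- **Recruitment.** Candidates are directed to the information sheet, eligibility criteria and consent form. To be included they must "have an Android or iOS smartphone and are willing or able to download the DrinksRation app". Being unwilling or unable to download it is an exclusion.
- **Intervention.** Those allocated to the app are emailed a link to it and asked to use it for at least 28 days.
- **Control.** Controls complete their surveys by email and "will be given access to the DrinksRation app at the end of the study period". The section acknowledges a structural difference between the arms and explains why no sham was used.
- **Adverse Events.** "The investigators will review the data weekly to identify any potential adverse events". Participants may also contact the researchers by study email or website.
- **Study Consent and Withdrawal.** Questions may be sent to the PI or investigators by email. "To withdraw from the control arm, participants will need to email the PI", whereas intervention participants withdraw inside the app.
- **Data Management and Confidentiality.** Data sit in REDCap or in the app, according to arm.

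**The concern.** Blinding participants means that they do not know which treatment they were allocated. The reason given here is that they were told the study consists of surveys. That could keep them from knowing what is being tested. It cannot keep them from knowing whether they received an app that they had to agree to download.

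This matters because the Statistical and Analysis Plan section defines the primary comparison on change in self-reported timeline follow-back units. A person who knows they have been given an alcohol-reduction app may report intake differently from a person who knows they have not. Randomization does not remove such a difference, and neither multiple imputation nor the mixed model can separate it from a true change in drinking. Participant blinding is the usual defence. A single-blind label tells readers, including the defence policy users for whom the trial is intended, that the defence is in place.

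The no-contact statement is a second, smaller problem. It is offered as part of the blinding of the research team, but other sections contradict it.

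**Working it through.** The finding rests on comparing sections. The only arithmetic is a check that the planned size does not depend on it.

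**1. Can participants be unaware of their arm?**

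| Stage | App arm | Control arm |
|---|---|---|
| Before consent (Recruitment) | Screened on willingness or ability to download the named app | Same |
| After allocation (Intervention, Control) | Emailed a link to the app; asked to use it for at least 28 days | Surveys by email; no app, no sham |
| Reminders (Control) | Push notification from the app | Email |
| Withdrawal (Study Consent and Withdrawal) | In the app's settings | Email to the PI |
| End of study (Control) | Already has the app | Given access to the app |

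Both arms start with the app named to them. From allocation onward the two experiences differ in the one feature under test. App-arm participants know they have it. Controls agreed to download it and receive only emailed surveys. What they were told about the purpose of the research leaves this unchanged.

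**2. Is there contact between participants and researchers?** Randomization and Blinding says none at any stage. Adverse Events gives participants a route to the researchers by email or website. Study Consent and Withdrawal gives them the PI's contact email for questions and requires controls to email the PI to leave. These statements cannot all be true.

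**3. What does a withdrawal email disclose?** App-arm withdrawal is managed entirely within the app, and control withdrawal goes by email to the PI. A withdrawal email therefore identifies its sender as a control. This covers only controls who choose to withdraw.

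**4. Does the weekly data review disclose arm?** Data location depends on arm, and the investigators review data weekly. If the reviewer can see which system a record came from, the arm is visible. The stated safeguard is role-based access to REDCap; the article does not describe access to data held in the app. Disclosure is possible but not shown.

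**5. Does the sample size change?** Study Sample gives a difference of 4 units/week, SD 14.9, 218 per arm and 40% attrition. The threshold of 0.05 is stated in the Statistical and Analysis Plan section. Power and sidedness are not stated; 80% and two-sided are assumed because they reproduce the figure.

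- n per arm = 2 × (1.960 + 0.842)² × 14.9² / 4² = 2 × 7.849 × 222.01 / 16 = 217.8, rounded up to 218.
- Allowing for attrition: 218 / (1 − 0.40) = 363.3, rounded up to 364 per arm, so 728 in total.

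Both stated figures reproduce, and neither uses the blinding status.

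**The case against.** The best defence is that the protocol is open about the difference between arms. The Control section calls it unavoidable, explains why a pared-down app would confuse interpretation, and cites heavy control-arm attrition when one was used before. Both arms complete surveys electronically on the same schedule, and no interviewer is described. All of this stands. It supports running the trial without a sham. It does not support calling participants blinded, because the section never draws the consequence for blinding.

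A reader might infer several stronger things that the documents do not support:

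- **That the research team is unblinded.** This is an inference. The article states a REDCap restriction and does not show the access rules for app data, so an undescribed firewall may exist. A withdrawal email shows the arm of a named person; the IMO holds the link between names and study codes, so the email does not by itself unblind a study record.
- **That the analyst is unblinded.** No section says who runs the primary analysis or whether arm codes are masked. That detail commonly sits in the analysis plan.
- **That the block size makes matters worse.** The article says "Two participant blocks in a 1:1 ratio will be used". Participants screen and consent online and REDCap allocates automatically, so no recruiter is described who could exploit a predictable sequence. Participants do not know their block.
- **That the Introduction's worry about under-reporting proves bias here.** That worry concerns AUDIT-C answers at dental inspections, where a low score avoids an intervention or referral. It does not describe a difference in timeline follow-back reporting between arms, and equal under-reporting in both arms would not create a spurious effect.
- **That the bias has a known size.** The documents give no figure for differential reporting, so any value set against the 4-unit target would be pure assumption.

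**Conclusion.** The participant-blinding claim is wrong as written. It is contradicted by the article's own eligibility, intervention and control sections, and it affects all 728 planned participants (364 per arm) on a self-reported primary outcome. At most, participants may be unaware of the hypothesis. This conclusion assumes only that participants read the eligibility criteria they are directed to and notice whether the app is sent to them.

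The no-contact statement is also contradicted, and withdrawal emails to the PI disclose arm for the controls who send them. Wider disclosure to the research team is possible but depends on access rules not shown.

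The consequence lies in what the trial can claim. A between-arm difference will be a difference in reported intake among people who know their arm. Neither the size nor the direction of any reporting bias can be derived from the documents. The sample size is unaffected.

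**What to change.** 1. In the Abstract, Study Design, and Randomization and Blinding, describe the trial as open-label for participants. If the information sheet supports it, add that they were not told the hypothesis.
2. Word the primary conclusion as an effect on self-reported intake, and name differential reporting between arms as a risk of bias.
3. Correct the no-contact statement so that it agrees with the email routes in Adverse Events and in Study Consent and Withdrawal.
4. Send control-arm withdrawal emails to the IMO, who is already unblinded, instead of the PI.
5. State who in the research team can see arm-identifying data, including app-held data and the weekly review, or restrict that access.

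The cost is revised wording, a mailbox redirect, a little extra work for the IMO, and a slightly less favourable design label. The sample size, outcome, model and randomization scheme need no change on this account.
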